### Economic assessment

The economic evaluation will be done over 12 months.

The result will be the quality-adjusted life year (QALY), derived from the l’EQ5D-5L questionnaire, as recommended by the French National Authority for health (HAS) [18].

#### Cost estimation

Direct medical costs will be calculated for each patient regarding the Diagnosis Related Group (Groupe Homogène de Séjour in French). Additional costs (resuscitation, intensive care, etc.) and non-reimbursed molecules will be considered in addition to the hospital stay. We will also estimate the direct costs related to complications of hospitalization. Nursing care and stoma replacement costs will also be estimated for stoma patients.

Indirect costs like work interruption will be estimated regarding the number of days not worked. A daily allowance will be estimated. Transports costs will include transport type, frequency and distance calculated according to the national health insurance rate in France.

Other costs will not be measured, but will be indirectly included in the Qaly measurement.

All costs will be calculated and presented in Euros (€) regarding current national health insurance rates in France.

#### Utility measure

QALY will be derived from the EQ5D-5L questionnaire. The EQ-5D-5Luestionnaire will be filled at 6, 12, 26 and 52 weeks after primary surgery. For patients benefiting from a continuity restoration, analyses will be performed on the cumulative data of the two interventions.

To avoid overestimating or underestimating patients’ utility, it will be estimated that this utility evolves in a linear way taking into account the time between each visit for each patient in the two groups.

Therefore, QALYs will be calculated as the utility × time interval between measures.

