### Endpoints

The primary endpoint is the 1 year overall morbidity, i.e., the number of patients who develop at least one complication (medical or surgical) at the 12-month follow-up.

All complications occurring during hospitalization will be collected. Late complications occurring after hospitalization will be collected during follow-up.

A 12-month endpoint was chosen because 50% of patients will require stoma closure 3–4 months after emergency surgery. In addition, some complications related to the realization of a protective stoma can occurred in the long-term (incisional hernia for example).

Secondary endpoints are the 90 days mortality; number of re-admissions and re-operations (other than for stoma closure); Incisional Surgical Site Infections (SSIs); Organ/space SSIs; Wound disruptions; Anastomotic leaks; Operating time; Intensive Care Unit (ICU) length of stay; total duration of hospital stay; number of patients with a stoma at 12 months after initial surgery; quality of life (QoL) assessed by the Short Form Health Survey (SF-36) [15], the Gastrointestinal Quality of Life Index (GIQLI) [16] and the EuroQol Five-levels (EQ-5D-5 L) (i.e., utility values for health states) [17] at baseline 6, 12, 26 and 52 weeks after primary surgery. A 12-month cost-utility analysis, will be also performed. For patients benefiting from a restoration of continuity, the analyses will be performed on the cumulative data of the two interventions.

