### Statistical analysis

Primary and secondary endpoints will be analyzed on an intention to treat basis. Data will be described overall and by randomized intervention group (protective stoma or no protective stoma) using standard parameters, i.e., mean, median, standard deviation, range and interquartile range for quantitative variables, and frequencies and percentages for categorical variables.

The main outcome being dichotomous, i.e., complication after surgery (yes/no), Pearson’s chi-square test or Fisher’s exact test will be used as appropriate to compare the two intervention arms 12 months postoperatively. Point and (exact if necessary) 95% confidence interval estimates of the proportions of complications in each arm will be calculated.

Use of the unadjusted test will be complemented by an adjusted comparison using the logistic regression model in order to adjust for center and possible prognostic characteristics.

The same general approach as outlined above will be used for secondary dichotomous outcomes (e.g., reinterventions, wound disruption, anastomotic leak). Regarding quantitative outcomes (e.g., operating time, length of postoperative hospital stay), comparison between the two intervention arms will be performed using Student’s test (or Mann–Whitney’s non parametric test as appropriate).

Quality of life scores will be described at each visit and compared between intervention groups at baseline and longitudinally during the study period using mixed linear models for repeated measures.

The overall survival at 3 months after surgery will be estimated using Kaplan–Meier survival curves and comparisons will rely on the logrank test.

The usual two-sided 0.05 level will be used for intervention comparisons.

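### The QALY formula does not say that the mean of the two adjoining utilities is meant, and the economic section's EQ-5D-5L schedule omits the baseline that the Endpoints section includes

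*Protocol article*

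**What the plan says.** All places are in the protocol article.

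- **Horizon** (Economic assessment): "The economic evaluation will be done over 12 months".
- **Assumption** (Utility measure): "it will be estimated that this utility evolves in a linear way taking into account the time between each visit". The stated reason is to avoid error in either direction in patients' utility.
- **Formula** (next paragraph of the same section): "Therefore, QALYs will be calculated as the utility × time interval between measures".
- **Schedule in the economic section** (Utility measure): the questionnaire "will be filled at 6, 12, 26 and 52 weeks after primary surgery".
- **Schedule in the Endpoints section**: the EQ-5D-5L, glossed as "i.e., utility values for health states", is listed with the SF-36 and GIQLI "at baseline 6, 12, 26 and 52 weeks after primary surgery".
- **Analysis** (Statistical analysis): quality-of-life scores are to be "compared between intervention groups at baseline and longitudinally during the study period using mixed linear models for repeated measures".
- **Use** (Incremental cost-utility ratio section): the ratio is formed at 12 months from each arm's mean cost and mean utility. Cost and utility pairs are resampled 1000 times for the acceptability curves.

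**The concern.** Under linear change, an interval has a utility at each end, and its QALY contribution is the mean of the two times its length. The printed formula has one unnamed utility. Three calculations fit its wording (start value, end value, mean), and only the mean agrees with the linear assumption. A one-ended value is a step function. It brings back the over- or underestimation that the linear assumption is meant to prevent whenever utility is changing, as it will be after emergency surgery.

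The schedule is a separate gap. Intervals between measures at weeks 6, 12, 26 and 52 begin at week 6. Without a baseline value, a linear rule gives nothing for the six weeks straight after surgery.

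The QALY difference is the denominator of the cost-utility ratio and enters every bootstrap replicate. If the rule is left open, an analyst has to choose it, possibly after seeing the data.

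**Working it through.** The article states no utility or QALY value, so there is no figure of its own to reproduce. The sample size does not bear on this point.

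**1. Formulas.** Let d(t) be the mean utility without stoma minus the mean utility with stoma at week t, and take 52 weeks as one year. The intervals are 6, 6, 14 and 26 weeks. Each rule is linear in the utilities, so the QALY difference depends only on d.

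- Linear change (mean of both ends): [3·d(0) + 6·d(6) + 10·d(12) + 20·d(26) + 13·d(52)] / 52
- Start value: [6·d(0) + 6·d(6) + 14·d(12) + 26·d(26)] / 52
- End value: [6·d(6) + 6·d(12) + 14·d(26) + 26·d(52)] / 52
- Linear, week 6 onwards only: [3·d(6) + 10·d(12) + 20·d(26) + 13·d(52)] / 52

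The linear result is the average of the start and end results, so the one-ended rules err by equal amounts in opposite directions. All three agree if d is the same at every time point.

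**2. Assumed utilities at weeks 0/6/12/26/52.** These are assumptions, not figures from the article.

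| Set | With stoma | Without stoma | d |
|---|---|---|---|
| 1 | 0.30/0.60/0.65/0.80/0.85 | 0.30/0.72/0.78/0.83/0.85 | 0/0.12/0.13/0.03/0 |
| 2 | 0.30/0.65/0.70/0.75/0.85 | 0.30/0.75/0.80/0.85/0.87 | 0/0.10/0.10/0.10/0.02 |
| 3 (smaller effect) | 0.30/0.70/0.74/0.78/0.85 | 0.30/0.75/0.80/0.83/0.85 | 0/0.05/0.06/0.05/0 |
| 4 (early harm without stoma) | 0.30/0.72/0.74/0.76/0.85 | 0.30/0.68/0.78/0.84/0.86 | 0/−0.04/0.04/0.08/0.01 |

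**3. QALY difference by rule** (change from the linear rule in brackets).

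| Set | Linear, from baseline | Start value | End value | Linear, from week 6 |
|---|---|---|---|---|
| 1 | 2.62/52 = 0.0504 | 3.32/52 = 0.0638 (+27%) | 1.92/52 = 0.0369 (−27%) | 2.26/52 = 0.0435 (−14%) |
| 2 | 3.86/52 = 0.0742 | 4.60/52 = 0.0885 (+19%) | 3.12/52 = 0.0600 (−19%) | 3.56/52 = 0.0685 (−8%) |
| 3 | 1.90/52 = 0.0365 | 2.44/52 = 0.0469 (+28%) | 1.36/52 = 0.0262 (−28%) | 1.75/52 = 0.0337 (−8%) |
| 4 | 1.89/52 = 0.0363 | 2.40/52 = 0.0462 (+27%) | 1.38/52 = 0.0265 (−27%) | 2.01/52 = 0.0387 (+6%) |

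Carrying the week 6 value back to week 0, instead of dropping those weeks, adds 3·d(6)/52. With d(0) = 0 this is the same size of error with the opposite sign; in set 2, for example, the difference becomes 0.0800 (+8%).

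**4. Weight of the undefined period.** Weeks 0 to 6 are 6/52 = 11.5% of the horizon.

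**5. Chance imbalance at baseline.** A between-arm difference of 0.10 in baseline utility adds 3 × 0.10/52 = 0.0058 to the linear QALY difference. That is 8% of the set 2 result (0.30/3.86) and 16% of the set 3 result (0.30/1.90). A comparison of unadjusted arm means carries this imbalance into the ratio.

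**The case against.** The strongest reply is that this is loose wording in a condensed article. The formula is presented as the consequence of the linear assumption, and mean utility times interval satisfies both sentences exactly. Nothing in the text names a start or end value, and the stated purpose argues against one. This stands: a reader might infer that the section contradicts itself, and it does not. What remains is that the article chose to print a formula and left out the word that makes it follow from its premise.

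A reader might also infer that the first six weeks have no starting value at all. The document as a whole does not support that. The Endpoints section plans a baseline EQ-5D-5L, and the Statistical analysis section compares quality-of-life scores at baseline. The defect is that the two schedules differ, and the incomplete one is in the section that defines the QALY.

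The percentages are open to the objection that every utility is assumed and that the article adopts neither one-ended rule. That is correct. They show how much the choice of reading can matter, not an error the trial will make.

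Nor should one infer that the last interval dominates the result because it is half the year. The ratio uses the difference between arms, and under the linear rule that interval supplies 13·[d(26) + d(52)] of the total: 0.39/2.62 = 15% in set 1 but 1.17/1.89 = 62% in set 4. The article gives no basis for choosing between them.

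**Conclusion.** The point holds as a gap in specification with a mismatch between two schedules. The formula does not name the utility its own linear assumption requires, and the economic section's list of assessments lacks the baseline given in the Endpoints section. Followed literally, the section covers weeks 6 to 52 of a 12-month horizon and permits a step rule at odds with linear change.

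Under the four assumed sets, a one-ended rule shifts the QALY difference by about 19% to 28% either way, and leaving out weeks 0 to 6 shifts it by about 6% to 14%. Both ranges rest on the assumed utilities, including equal baseline values in the two arms. If the intended rule is the mean of adjoining values from baseline, neither shift arises and only the text needs correcting.

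The reach is limited to a secondary economic outcome. The primary endpoint, the sample size and the clinical comparisons are unaffected.

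**What to change.** Three changes to the economic sections:

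1. **Formula** (Utility measure): QALY = sum over intervals of [(utility at start + utility at end)/2] × interval in years, from baseline to week 52, using each patient's actual visit dates.
2. **Schedule** (Utility measure): add baseline to the EQ-5D-5L time points so that they match the Endpoints section.
3. **Comparison** (Incremental cost-utility ratio section): estimate the between-arm QALY difference adjusted for baseline utility, and use it in the ratio and in each bootstrap replicate. This improves on the unadjusted arm means now described rather than correcting an error in them.

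The cost is a few sentences and slightly more analysis work, since the adjustment has to be refitted in each of the 1000 replicates. No new data collection is needed, because the Endpoints section already plans the baseline questionnaire. The change should be made before the economic data are analysed, so that the rule is not chosen after the results are seen.

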#### Medico-economic analysis

##### Cost-utility analysis

A cost and utility description of each group will be presented. Utility calculus will be presented in number of Qalys generated by each strategy. Mean and standard deviation with the 95% confidence interval will be estimated for each group.

##### Incremental cost-utility ratio (ICER) calculation and analysis

The incremental cost-utility ratio will be calculated at 12 months for the intervention group (strategy 1) versus the control group (strategy 2) with the mean costs and utility regarding each strategy. The incremental cost-utility ratio will be presented in additional cost per year of life saved (one QALY equates to 1 year in perfect health).

Sampling uncertainty around the cost estimates will be investigated using nonparametric bootstrapping. Re-sampling cost and utility pairs from the original sample will be used to generate 1000 replicates of mean differences in cost and utility. The resulting scatter plot will be used to derive cost-effectiveness acceptability curves (CEAC) by calculating the proportion of ICER replicates which would be considered cost-effective at various thresholds of willingness-to-pay (WTP) for an additional QALY.

### Data collection and monitoring

Data of each patient are collected via an electronic Case Report Form (eCRF) (base line, perioperative and long-term data), and all eCRFs are gathered by the coordinating center, Rouen University hospital.

After the initial surgery, all patients will be examined at 6, 12, and 26 weeks, in the surgical department where they were operated; a final study visit will be carried out 12 months (evaluation of primary endpoint) after surgery. The parameters explored at medical examinations are: occurrence of complications and quality of life assessment.

The entry of data are performed using Ennov Clinical® software (Ennov Group, [name]). The database will be analyzed by the Biostatistics Unit of the University Hospital of Rouen.

During study conduct, the sponsor will conduct periodic monitoring visits to ensure that the protocol and Good Clinical Practices (GCPs) are being followed. The monitors may review source documents to confirm that the data recorded on CRFs is accurate.

This trial is registered on clinicaltrials.gov. The status is in progress: the first inclusion was June 15th, 2021.

## Discussion

This trial focuses on a surgical procedure for the treatment of diverticulitis peritonitis, one of the most commonly diagnosed surgical emergencies world-wide.

Although the Hartmann procedure was longtime considered as the gold standard for emergency surgery in diverticulitis, there is now a lot of data reporting significantly improved morbidity and mortality rates following resection and primary anastomosis. However the role of proximal diversion under these circumstances remains unclear. At present, there is no evidence-based medicine concerning the role of the protective stoma; current practice being essentially guided by old habits.

In fact, surgical removal of the pathologic process and control of sepsis remains the cornerstone of treatment for patients with perforated diverticulitis. Current surgical efforts should be to minimize the burden of operation with avoidance of creating a stoma and improving cosmesis without compromising the safety and efficacy of the procedure.

Obviously, defunctioning stoma reduces symptomatic anastomotic leakage after anterior resection of the rectum and is therefore recommended in rectal cancer resection with low anastomosis [19].

However, population of patients presenting with diverticulitis is different from that with rectal cancer: patients don't have a history of pelvic radiotherapy and the anastomosis is high. Resection and primary anastomosis without protective stoma is a recent and interesting approach in the management of diverticulitis peritonitis. However, this important topic has never been assessed in a randomized multicenter manner.

The low incidence of complications found in studies reporting this approach leads us to believe that protective stoma formation is not necessary in cases without obvious risk factors and when the general principles of a good anastomosis are followed. Our belief that stomas should be performed only in selected cases based on fact that stomy is not free of complications. Even more, if the surgeon feels that the anastomosis has major problems, conversion to terminal colostomy (Hartmann's operation) could be the best solution for the patient.

The DIVERTI 2 trial aims to test the hypothesis that sigmoidectomy with primary anastomosis without protective lateral stoma provides significant benefits in terms of reduced postoperative morbidity compared to conventional sigmoidectomy with primary anastomosis with a protective lateral stoma for peritonitis Hinchey III and IV due to perforated diverticulitis.

We believe that sigmoidectomy without protective lateral stoma can be a treatment option, since this technique allows preservation of normal intestinal continuity avoiding a protective stoma.

These patients may benefit from a lower rate of postoperative cumulative morbidity. In addition, impairment of quality of life in stoma carriers will be avoided without affecting functional outcome.

According to a lower rate of postoperative morbidity and the fact that closure of the stoma following surgery is not necessary, a reduction in direct costs (hospital stays and hospital admissions) may be expected. The introduction of sigmoidectomy without protective lateral stomy may likely be adopted in the future on a larger scale.

The DIVERTI 2 trial would be the first to study the role of protective stoma in patients with peritonitis Hinchey III and IV due to perforated diverticulitis who are candidates for sigmoidectomy with primary anastomosis.

It would also be the first study to evaluate the costs of protective stoma, and its impact on patient QoL.

## Data Availability

The study protocol is available on the website clinicaltrials.gov at the URL: https://clinicaltrials.gov/ct2/show/NCT04604730?recrs=a&cond=Diverticulitis&draw=2&rank=12. All data regarding ethical aspects are available at the Unité de Recherche Clinique—CHU Charles Nicolle. The materials that will be generated in this study will be available on request from the corresponding author.

## Abbreviations

ANSM: National Drug Agency
ASA: American Society of Anesthesiology
CPP: People Protection Committee
CT: Computed Tomography
DS: Defunctionning stoma
eCRF: Electronic Case Report Form
EQ-5D-5L: EuroQol Five-levels
GCPs: Good Clinical Practices
HAS: French High Health Authority
ICUR: Incremental cost-utility ratio
IPD: Individual Participant-level Data
LOS: Length of stay
PHRC: National Clinical Research Program
QALY: Quality Adjusted Life Year
QoL: Quality of life
SSI: Surgical Site Infections
